**Methods/Design:**

Ninety-two patients will be randomized into four groups to receive transcranial direct current stimulation (real/sham) + transcutaneous electrical nerve stimulation (real/sham) for 12 sessions over a period of four weeks. The primary clinical outcome (pain intensity) and the secondary ones (sensory and affective aspects of pain, physical functioning and global perceived effect) will be recorded before treatment, after four weeks, in Month 3 and in Month 6 after randomization. Confounding factors such as anxiety and depression, the patient’s satisfaction with treatment and adverse effects will also be listed. Data will be collected by an examiner unaware of (blind to) the treatment allocation.

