## Methods/Design

A controlled factorial (2 × 2) clinical trial will be conducted to evaluate the analgesic efficacy of cerebral and peripheral stimulation in chronic low back pain (Figure 1).

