### Sample size

The sample size was *a priori* estimated by the analysis of power [50] to detect a clinically important minimal difference (10% reduction from the baseline) in the outcome of pain intensity measured by the Numerical Rating Scale for Pain [51]. The effect size and the probability of error type 1 (α) and type 2 (β) were 0.33, 0.05 and 0.20, respectively. According to the data of sample calculation, there must be a total of 75 participants. However, considering 20% of sample loss, a sample size of 92 participants (23 per group) was calculated.

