### Statistical analysis

All statistical procedures will be performed according to the principles of intention to treat. Linear mixed models will be used to identify intra- and inter-group differences at the end of treatment and in Month 3 and Month 6 of follow-up. All data will be analyzed using software SPSS v.20 for Windows. The level of significance is 0.05.

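### The 92 randomized do not keep the required 75 after the stated 20% loss: 73.6 remain, and 92 covers a loss of at most 18.5%

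*Protocol article*

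**What the plan says.** The Sample size section sets out the inputs: "The effect size and the probability of error type 1 (α) and type 2 (β) were 0.33, 0.05 and 0.20, respectively". From these it concludes that "there must be a total of 75 participants". It then allows for attrition: "considering 20% of sample loss, a sample size of 92 participants (23 per group) was calculated". The abstract repeats the total ("Ninety-two patients will be randomized into four groups"), and so does the section on participants and eligibility.

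The section does not give the formula for the loss allowance, the type of effect size, the test behind the 75, or the time by which the 20% loss is expected.

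Three other places bear on the point. The design is given as "A controlled factorial (2 × 2) clinical trial will be conducted". The Objective section places the primary analysis of pain intensity at four weeks after randomization. The Statistical analysis section states "All statistical procedures will be performed according to the principles of intention to treat" and names linear mixed models covering the end of treatment, Month 3 and Month 6.

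**The concern.** An allowance for loss should leave the required number in the analysis once that loss has occurred. The required number, the loss fraction and the number randomized are all printed here, so the reader can check them directly, and they do not agree. A total of 92 less one fifth falls short of 75.

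What is at stake is modest. A reader, or whoever monitors attrition, will take it that the trial can lose 20% of its patients and still meet its own target. By its own figures it cannot. The target also has no slack: under the test that reproduces it, 75 is the smallest total that reaches 80% power.

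**Working it through.** **Inputs** (Sample size section unless noted)
- Required total: 75
- Loss allowance: 20%
- Randomized: 92, as 4 × 23
- Effect size 0.33, α = 0.05, β = 0.20
- Four cells in a 2 × 2 factorial (Methods/Design)

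**Step 1. Reproduce the 75.** The test is not stated, so candidate readings were tried. Power was taken from the noncentral F distribution with four cells, denominator degrees of freedom N − 4 and noncentrality N × f².
- 0.33 as Cohen's f, 1 numerator degree of freedom: smallest N with power of at least 0.80 is 75 (power 0.805).
- 0.33 as Cohen's f, 3 numerator degrees of freedom: smallest N is 105.
- 0.33 as a standardized difference between two means: 145 per arm.

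The first reading matches exactly. It is also a natural one for this design, where each main effect and the interaction has one degree of freedom.

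**Step 2. Reproduce the 92.** 75 × (1 + 0.20) = 90, and the next multiple of four is 92, or 23 per group. This matches the printed figure, so the allowance was probably added to the target. That is an inference from the match.

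**Step 3. Check the 92 against the 75.**
- Remaining after 20% loss: 92 × 0.80 = 73.6, or 18.4 per group.
- Shortfall: 75 − 73.6 = 1.4 participants.
- Largest loss that 92 can absorb: 1 − 75/92 = 18.5%. In whole patients this is 17, whereas 20% of 92 is 18.4.

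**Step 4. Number needed for 20% loss.**
- 75 / (1 − 0.20) = 93.75, so 94 in total.
- In four equal groups: 96 (24 per group), leaving 96 × 0.80 = 76.8.
- The plan is therefore 2 short in total, or 4 short with equal groups.

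**Step 5. Effect on power** (f = 0.33, 1 numerator degree of freedom, four cells)

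| N analysed | Power |
|---|---|
| 73 | 0.794 |
| 73.6 | 0.797 |
| 74 | 0.799 |
| 75 | 0.805 |
| 92 | 0.879 |

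If the full 20% is missing from the primary analysis, power goes from 80.5% to about 79.7%, a loss of 0.8 percentage points.

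**The case against.** **The allowance may mean a 20% add-on.** With no formula given, the phrase could mean adding 20% to the required number: 90, rounded up to 92. Worked by group, 75/4 rounds up to 19, and 19 × 1.2 = 22.8, so 23. On that reading the figures follow from one another. This probably explains how 92 arose. It does not make the statement sound, because loss is counted from those enrolled, and a reader will take the trial to withstand 20% attrition.

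**The gap is within rounding of the effect size.** An effect size printed as 0.33 could lie anywhere from 0.325 to just under 0.335. Under the same test the required total is 77 at f = 0.325 and 73 at f = 0.3349, and at f = 0.332 a total of 73.6 already gives 80.2% power. This stands as a point about materiality: the inputs are not precise enough to separate 79.7% from 80%. It does not remove the conflict, since the article itself fixes the requirement at 75.

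**Lost patients may still contribute.** The primary assessment is at four weeks, while follow-up runs to Month 6. A patient lost after week four has already given the primary outcome and stays in the mixed model. The article does not say whether the 20% is meant by week four or over the whole six months. This stands too, and makes the power loss conditional.

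**A stronger reading does not hold.** A reader might infer that the trial is underpowered, or will certainly fall below 80%. The documents do not support that. The shortfall arises only if more than 18.5% are lost before the primary assessment. With all 92 contributing, power in the same test is 87.9%. The percentages also rest on a test that was inferred.

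**Conclusion.** The point holds as a small arithmetic inconsistency. No formula in an unseen document can make 92 × 0.80 reach 75, and nothing elsewhere in the article changes the three figures.

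The conflict between the figures needs only one assumption, that loss is counted from those randomized. The power figures need two more: that the test is the one-degree-of-freedom F test with f = 0.33, and that the entire loss falls before week four. Whether 92 came from multiplying by 1.20 is likely but not documented, and the conclusion does not depend on it.

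The validity of the trial, its conduct and the interpretation of its results are not affected.

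**What to change.** Keep 92 and correct the stated tolerance. Suggested wording for the Sample size section: *Randomizing 92 patients, 23 to each arm, leaves the required 75 if no more than 18% are lost by the four-week primary assessment.* This also settles the time point to which the allowance refers.

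No power figure needs to be added. If one is wanted for 20% loss, it should be given as about 79.7%, with the test and the effect-size measure named; rounding it down to 79% would understate it.

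The alternative is to keep the 20% allowance and raise the total to 94, or 96 for equal groups. For a gain of under one percentage point of power, that is not worth the extra recruitment. The recommended change costs one sentence and no patients.

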### Statistical analysis

All statistical procedures will be performed according to the principles of intention to treat. Linear mixed models will be used to identify intra- and inter-group differences at the end of treatment and in Month 3 and Month 6 of follow-up. All data will be analyzed using software SPSS v.20 for Windows. The level of significance is 0.05.

## Discussion

According to our review, this is the first randomized double-blind clinical trial to investigate the analgesic efficacy of transcranial direct current stimulation (tDCS) combined with transcutaneous electrical nerve stimulation (TENS) in patients with chronic nonspecific low back pain. The factorial design used in this study will allow three interventions to be evaluated simultaneously: cerebral stimulation, peripheral stimulation and combined stimulation. Furthermore, the use of sham tDCS and sham TENS represents a more robust experimental design to control the placebo effects. The results of this study will provide important information for clinical practice and conservative management of chronic low back pain. The possibility of synergistic and additive effect of these noninvasive, nonpharmacological, well-tolerated techniques presenting minimal adverse effects can turn them into a promising therapeutic tool for health professionals, improving the health status of the population and reducing the socioeconomic consequences of chronic low back pain.
